### Project management

The trial will be run on a day-to-day basis by the Project Management Group (PMG), which reports to the Trial Steering Committee (TSC). The TSC receives recommendations related to the data arising from the trial from the Data Monitoring Committee (DMC). The PMG will consist of the Chief Investigator, Clinical Trials Unit Director, Head of Operations, Senior Trials Manager, Trial Programmers, the Trial Statistician and Trial Administrator. The PMG will meet every 3 to 4 weeks. The TSC and DMC will consist of independent clinical and statistical experts, as well as parent and public representatives. The TSC and DMC will meet three times over the course of the trial; charters are available by contacting the study team. Both are independent from the sponsor. The trial will be run according to the Clinical Trials Unit standard operating procedures, including potential audit. The sponsor is the University of Oxford ([contact]), which has ultimate authority over the trial’s scientific integrity.

### Patient and public involvement

National charity for sick and preterm babies, Bliss, has been a co-applicant for the study since its inception. A total of 675 people who had experience of premature birth were involved in initial online engagement work to define the most important outcomes for the RCT, give their thoughts on ethical issues and share the ways in which they found information about lactation to inform the dissemination plan. From this pool of parents, six also attended virtual panels to give detailed feedback on trial design and participant-facing documents, and a further 12 took part in an exercise to advise on modifications to the intervention recording. Modifications were made to the intervention recording in three key areas raised by parents—minimising a feeling of pressure on volumes of milk expressed, sensitive language related to potentially traumatic birth and language appropriate to immature and potentially sick infants. Bliss and a parent contributor are members of the Trial Steering Committee.

### Statistics and analysis

#### Sample size and power calculation

In the most relevant previous study [25], mean expressed milk yield at day 14 of the trial increased from 318 ml (standard deviation; SD 309 ml) to 862 ml (SD 309 ml) with the use of a visualisation/relaxation soundtrack. Initial exploratory work suggested that baseline milk yield in the recruiting sites is higher than this, and therefore, this study is powered to detect an increase in highest 24-h expressed milk yield from 670g (SD 300g) to 825g (SD 300g), with 80% power and a two-sided significance level of 0.05. This is a 155g absolute mean difference or a 0.5 standardised mean difference. In total, 118 participants are required, so the recruitment target was set at 132 to allow for 10% attrition. Since breastmilk has an average specific gravity of 1.03 [62, 63], 670g is estimated as equivalent to 650ml and 825g is estimated as equivalent to 800ml, although much of the literature views volume and mass measurements as interchangeable for breastmilk [64–66].

#### Description of statistical methods

Demographic and clinical data will be summarised with counts and percentages for categorical variables, means (with SDs) for normally distributed continuous variables and medians (with interquartile or simple ranges) for other continuous variables.

Statistical analysis of continuous outcomes will use linear regression with adjusted and unadjusted mean differences presented, or quantile regression with median differences presented, as appropriate. Binary outcomes will be analysed using log binomial regression, or Poisson regression with a robust variance estimator if the model fails to converge, and risk ratios will be presented. 95% confidence intervals will be presented.

Analyses will be adjusted for the stratification factors (recruiting neonatal unit, gestational age at birth and whether the participant has one or two babies alive at randomisation) where possible. The STAI score at day 21 will be adjusted for the STAI score at baseline. The primary outcome will be adjusted for the associated measurement day of the highest milk weight. Both crude and adjusted estimates will be presented, but the primary inference will be based on the adjusted estimates. Further process indicators, such as number of direct breastfeeds, will be summarised by randomised arm, with no comparative statistics presented.

Participants will be analysed in the groups to which they were randomly assigned, comparing the outcome of all participants allocated to intervention with all those allocated to the comparator group, regardless of deviation from the protocol or treatment received (the Intention to Treat population). Analysis will take place on a superiority basis.

Exploratory subgroup analysis will use a statistical test of interaction to examine the effect of the intervention on the primary outcome by gestational age at birth (<28 weeks and ≥ 28 weeks). Stratified analysis by the other stratification factors described and exclusive breastmilk feeding intention at baseline will take place with no formal test for interaction. This is to limit multiple comparisons and due to the low statistical power for subgroup analysis.

An exploration of adherence effect on the primary outcome will be conducted, dividing the intervention group into high- and low-frequency adherence by their reported number of times listening to the recording. An exploration of perceived relaxation effect on primary outcome will be conducted, dividing the intervention group into those who report the intervention to be relaxing and those who do not (via Likert scale). Summary statistics will be presented, with no statistical inference.

Basic demographics of the recruited participants will be compared with aggregate data from the potentially eligible population with no statistical inferences made.

Primary analysis will take place on a complete case basis. If more than 10% of primary outcome data is missing, sensitivity analysis will be performed to explore the pattern of missingness for the primary outcome, using multiple imputation and/or a pattern mixture model as appropriate. Sensitivity analyses will also assess whether the definition of the primary outcome has led to bias by assessing the impact of using day 21 expressing yield only, and separately of excluding day 4 logs. Stata will be used for all analysis.

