## Background

There are an estimated 2.4 million infants born at less than 32 weeks gestation globally each year [1], and the rate of premature birth is increasing [2]. Complications arising from premature birth are the leading cause of neonatal death in the UK [3] and globally [2]. Premature infants also have increased risk of long-term disability, which increases as the gestational age at birth decreases [4]. Premature birth has a significant effect on parental mental health—systematic review estimates that 42% of parents have significant anxiety and 40% have significant post-traumatic stress reactions in the first month after birth [5]. Between 29 and 40% of mothers have depression in this timeframe [6]—all of these figures are higher than found after term, healthy birth [5, 6].

Infants born at less than 32 weeks gestation cannot fully orally feed from birth and are therefore given nutrition intravenously and/or directly into the stomach with an enteral tube. To provide breastmilk for their infants, mothers must express milk from the breasts for a prolonged period. Maximising the volume of maternal breastmilk given to these infants is associated with improved mortality, morbidity and long-term neurodevelopmental outcome [7–10]. Increasing the amount of breastmilk that mothers of very premature infants can express in the weeks after birth also leads to longer duration of breastmilk feeding [11, 12], with consequent well-known public health benefits for both infant and mother [13]. Breastmilk feeding is the provision of breastmilk by any route (for example, directly at the breast, by gastric tube or by bottle).

Despite motivation to provide expressed breastmilk for their infants, there is a high risk of poor milk supply, leading to non-exclusive breastmilk feeding [14–18] and an increasing failure to meet mothers’ own goals for breastmilk provision as time goes on [19]. It is challenging to establish and then maintain a full milk supply through exclusive expressing [20, 21], which is exacerbated when pregnancy has been abbreviated and the breast tissue and hormonal milieu are therefore not at an optimal stage. Perinatal interventions associated with premature birth may also pose lactation challenges—such as provision of antenatal steroids, which also delay milk ‘coming in’ [22] (lactogenesis II), and caesarean birth.

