**Fig. 1 Fig1:**
[figure not shown]
Trial summary flowchart

Data will be collected at six timepoints, described in Fig. 2 and Table 2. At baseline, the participant completes a case report form (CRF) questionnaire about themselves, their previous breastmilk feeding experience and feeding intentions (B1a). Research staff complete a trial entry CRF with information about the birth and infant’s medical status at randomisation (B1b). In the expressing phase of data collection, the participant completes a CRF questionnaire and 24-h log of expressed milk at three timepoints. E1 is day 4 after the infant’s birth (the day of birth is termed day 0). E2 is day 14 and E3 is day 21 after the infant’s birth. In the feeding phase of data collection, the participant responds to an SMS message asking about the infant’s feeding status, at two timepoints. F1 is at 36 weeks’ post-menstrual age (PMA; 4 weeks before the estimated date of delivery—the EDD—which defines 40 weeks of gestation) and F2 is at 18 weeks after the EDD—their SMS response automatically completes a CRF for each timepoint. If no SMS is received, infant feeding status can be extracted from the medical notes.

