### Randomisation

Participants will be randomised with a 1:1 allocation using stratified permuted block randomisation by a secure web-based randomisation programme hosted by the National Perinatal Epidemiology Unit Clinical Trials Unit. Stratification will be based on recruitment neonatal unit, gestational age at birth (23^+0^ to 27^+6^ weeks versus 28^+0^ to 31^+6^ weeks) and multiple birth (one versus two babies alive at time of randomisation). Research staff and the participant are aware of the allocation after randomisation, as the study is unmasked. Study identification numbers are not consecutive, to reduce the possibility of research staff monitoring the sequence of allocation.

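### The primary model takes its baseline covariates only from the stratification factors and adds post-randomisation measurement day, leaving collected prognostic baseline variables unused

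*Protocol article*

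**What the plan says.** Under Description of statistical methods, the protocol article fixes the adjustment set: "Analyses will be adjusted for the stratification factors (recruiting neonatal unit, gestational age at birth"), together with the number of live babies (one or two) when the mother was randomised, as far as this can be done. For the main endpoint it adds one more term: "The primary outcome will be adjusted for the associated measurement day of the highest milk weight". Crude and adjusted results are both to be shown, but the adjusted one carries the primary inference.

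Under Randomisation, the gestational stratum has two levels: "gestational age at birth (23^+0^ to 27^+6^ weeks versus 28^+0^ to 31^+6^ weeks". The analysis section does not say whether gestational age enters the model in these bands or as a continuous term.

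Under Aim and design, more is recorded at baseline than the model uses. The participant completes a "questionnaire about themselves, their previous breastmilk feeding experience and feeding intentions (B1a"), and "Research staff complete a trial entry CRF with information about the birth and infant’s medical status at randomisation (B1b"). The analysis section uses one of these items, but only to split the sample: a stratified analysis by "exclusive breastmilk feeding intention at baseline will take place with no formal test for interaction".

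The Background gives a reason to expect details of the birth to matter: "Perinatal interventions associated with premature birth may also pose lactation challenges". It gives antenatal steroids and caesarean birth as examples.

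**The concern.** Two features of the same adjustment set point the wrong way.

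First, baseline variables that plausibly predict milk yield are collected and left out. No milk yield from before randomisation is named: randomisation closes at midnight on day 3 and the first expressing log is on day 4. The usual strongest covariate, a baseline value of the outcome, is therefore not available, and other baseline information is worth more. The plan accepts the principle elsewhere, since day 21 STAI is adjusted for baseline STAI.

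Second, the one non-stratification term that does enter is not a baseline variable. The day of the highest weight depends on how yield develops after allocation and on which logs the participant returns. It is part of how the outcome is formed. If the recording helps mothers go on expressing, the peak may move to a later day. Conditioning on that day could then remove part of the effect or distort it.

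At stake are some precision, protection against chance imbalance with 59 per arm, and a headline estimate with a clear interpretation. Precision matters here because the target leaves no spare participants beyond 10% attrition, the primary analysis is complete case, and the section on participant remuneration reports higher than expected loss for the primary outcome.

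**Working it through.** **Inputs.** From Sample size and power calculation: means 670 g and 825 g (difference 155 g), SD 300 g, two-sided 5%, 80% power, 118 required, 132 recruited. From Randomisation: 1:1 allocation, so 59 per arm. Assumed: the partial R² of the added baseline covariates, meaning the share of residual variance that they explain. The documents give no value, so a range is shown.

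**The plan's own figure.** n per arm = 2 × (1.960 + 0.842)² × 300² / 155² = 58.8, rounded up to 59, so 118 in total. For attrition, 118 / 0.9 = 131.1, rounded up to 132. Both figures reproduce, and neither takes credit for covariates. With a t test on 116 degrees of freedom, power at 118 is 79.5% (80.1% by the normal approximation).

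**Effect of added covariates.** Residual SD = 300 × √(1 − R²). SE = residual SD × √(2/59). The 95% CI half-width is 1.96 × SE. Power is from the noncentral t distribution with noncentrality 155 / SE and 116 degrees of freedom.

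| Partial R² (assumed) | Residual SD (g) | SE (g) | CI half-width (g) | Power |
|---|---|---|---|---|
| 0 | 300.0 | 55.2 | 108.3 | 79.5% |
| 0.02 | 297.0 | 54.7 | 107.2 | 80.3% |
| 0.05 | 292.4 | 53.8 | 105.5 | 81.5% |
| 0.10 | 284.6 | 52.4 | 102.7 | 83.5% |
| 0.20 | 268.3 | 49.4 | 96.8 | 87.5% |

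**Cost of the extra terms.** The larger critical value costs under 0.1 point for three or four terms. Chance imbalance of q added covariates between the arms inflates the variance by about 115 / (115 − q). If the covariates explain nothing, power falls from 79.5% to 78.4% for q = 3 and to 77.3% for q = 6. Break-even is at R² = q / 115, which is 3/115 = 0.026 for three terms and 6/115 = 0.052 for six. Net of the three-term cost, the rows for 0.02, 0.05, 0.10 and 0.20 become 79.2%, 80.4%, 82.5% and 86.6%.

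**What the table leaves out.** It treats 300 g as the SD left after the stratification factors, and it compares models without measurement day. It gives no figure for any bias from conditioning on measurement day, because the documents give nothing from which to derive one.

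**The case against.** The best defence is that nothing here is invalid. Adjusting for the stratification factors matches the randomisation, the stated 118 and 132 do not depend on further covariates, and which prognostic terms to add is a matter of judgement. The analysis plan and full protocol are not shown and may add covariates or state how gestational age is coded. This largely stands: the omitted covariates are an efficiency point, and two-band coding in the model cannot be asserted. It does not remove the point, because the article itself lists the covariates, includes measurement day, and ties primary inference to that set.

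The size of the gain is also open to challenge. It rests on an assumed R², and at 0.02 the gain is cancelled by three added terms. If the stratification factors already explain 5–10% of the variance (also assumed), the planned model starts at 81.5–83.5% and not at 79.5%. If quantile regression is used, as the plan allows, these two-mean figures do not carry over directly. All of this stands and limits what can be claimed.

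Measurement day has a rationale: a mother who returns only a day 4 log gets a low maximum, and the day partly reflects that. But that is a missing-data problem. The planned sensitivity analyses (day 21 only, day 4 excluded, and methods for missing data) address it without conditioning on something the intervention may change.

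A reader might infer more than the documents support:
- **That the adjustment is free.** It costs degrees of freedom, and under complete-case analysis a missing baseline item could exclude a participant unless handled.
- **That these are the only prognostic variables available.** Baseline STAI and the infant's medical status are collected too, and the stratification factors are themselves prognostic candidates.
- **That mode of birth is on the trial-entry form.** The article says only that the form covers the birth.
- **That the gain would offset the excess loss to follow-up.** No loss figure is given, so this cannot be calculated.

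**Conclusion.** The point holds as a modest improvement in precision, together with the removal of one badly chosen covariate. The only baseline covariates named for the primary model are the stratification factors. Feeding experience and intention are collected and unused, and the extra term that is used arises after randomisation.

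On the assumptions above, the gain at 118 analysed runs from about 1 to 2 points of power at partial R² of 0.02–0.05 to 4 to 8 points at 0.10–0.20, less roughly 1 point for three added terms. With weak covariates the net effect is close to zero. It would be wrong to conclude that the trial is underpowered because of this choice or that adjusting for the stratification factors is a mistake. Whether measurement day would bias the estimate, and in which direction, cannot be settled from the documents. The objection is that it can be affected by allocation and sits in the model on which the primary inference rests.

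**What to change.** Before any comparative analysis, pre-specify the primary model with pre-randomisation terms only: arm, neonatal unit, number of babies, gestational age as a continuous term in place of the two bands, previous breastmilk feeding experience, and exclusive-feeding intention. Add mode of birth if the trial-entry form records it. Leave out measurement day and rely on the sensitivity analyses already planned for the timing question.

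State that a missing baseline item is filled by simple imputation, so that nobody with a primary outcome is lost from the complete-case analysis. Use the same covariates in any imputation model for the outcome. Confirm that the baseline questionnaire is completed before allocation is known: the schedule puts it in the same window as randomisation without giving the order, and stated intention could shift in an unmasked trial.

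The cost is wording in the analysis plan, a rule for missing baseline items, and about three model terms, partly offset by dropping measurement day. No new data are needed, and the sample size is unchanged. If the analysis plan already contains such a set, the two documents need only be aligned.

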**Fig. 2 Fig2:**
[figure not shown]
Timepoints for trial data collection

**Table 2 Tab2:** Schedule of trial procedures

Procedures	From the day of birth (day 0) up to midnight on day 3 of life	Day 4, 14 (E1 & E2)	Day 4 to 7	Day 21 (E3)	32 weeks post-menstrual age ***(exploratory timepoint)***	36 weeks post-menstrual age (F1), 9 and 18 weeks after estimated date of delivery (F2)
					*Only applies if infant born at <27 weeks gestation*	*In the abbreviated follow-up period the trial completes at F1*
Informed consent	✔					
Eligibility assessment	✔					
Randomisation	✔					
Baseline Questionnaire	✔					
Maternal training and assessment on use of scales	✔					
Check-in and verify accurate use of scales			✔			
Questionnaire & 24-h expressing log		✔		✔		
Maternal mental health questionnaires				✔		
Text message response					✔	✔

Two further exploratory data collection timepoints will take place, which do not contribute data to the RCT, but to exploratory analyses. These are a 24-h expressing log and questionnaire CRF at 32 weeks PMA, for participants who had given birth at less than 27 weeks PMA; and a feeding assessment SMS message at 9 weeks after the EDD. For example, an infant born at 24 weeks of gestation is 8 weeks old at 32 weeks PMA and 25 weeks old at 9 weeks after the EDD.

The trial forms part of a doctoral thesis. For reasons of efficiency within the available time, the recruitment period is divided into two sections. The majority of recruitment (10 months) will take place in the ‘complete follow-up’ period where participants will receive both F1 and F2 SMS messages. The final 22 weeks of recruitment will form the ‘abbreviated follow-up’ period where participants will receive only the F1 SMS message.

The time from recruitment to the end of the expressing phase of the study is 3 weeks. The time from recruitment to the end of the feeding phase of the study varies with the gestation of the infant and the follow-up period. The longest possible time—for a participant recruited in the ‘complete follow-up’ period with an infant born at 23 weeks—will be 35 weeks. The shortest possible time—for a participant recruited in the ‘abbreviated follow-up’ period with an infant born at 31 weeks and six days—will be 4 weeks. Figure 3 shows sample timelines for the most and least premature infants.

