### Secondary outcomes

The following secondary outcomes will be reported:Proportion of participants expressing at least 750g of milk in 24 h on any of day 4, 14 or 21 (E1, E2 or E3)Rate of milk expression (in grams per minute) at day 21 (E3)Average Spielberger State Trait Anxiety Index (six-item format; STAI-6) score at day 21 (E3)Average Post-traumatic Stress Checklist for DSM-5 (PCL-5) score at day 21 (E3)Proportion of participants feeding their infant/s only breastmilk (no infant formula) at 36 weeks PMA (F1)Proportion of participants feeding their infant/s any breastmilk at 36 weeks PMA (F1)Proportion of participants feeding their infant/s only breastmilk (no infant formula) at 18 weeks after the estimated date of delivery (4 months corrected age—F2)

The STAI is a reliable measure of anxiety [47] and widely used, including in studies after very premature birth [48, 49] and after use of a relaxation intervention in the neonatal intensive care unit [27]. The original STAI is a 20-item questionnaire with four answer options for each question (‘not at all’, ‘somewhat’, ‘moderately’ or ‘very much’). The total score range is 20–80, with higher scores signifying more anxiety, <36 generally considered normal [50] and ≥40 signifying clinically significant anxiety [48] (although this cut off varies across the literature [5]). The shortened STAI-6 contains a subset of six questions, giving a score total of 6–24, which are then scaled to 20–80 for comparability [51]. The short form is highly correlated with the 20-item STAI, with internal consistency greater than 0.9 [52]. The minimal meaningful difference in STAI score has been suggested as 10 [53].

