The PCL-5 is a commonly used [54] publicly available screening assessment for post-traumatic stress disorder (PTSD) aligned to the Diagnostic and Statistical Manual of Mental Disorders-Fifth Edition (DSM-5) [55]. It has been used in the context of birth related trauma [56]. The PCL-5 is very similar to the Impact of Event Scale (IES) and the preceding PCL for DSM-IV that have both been used in the specific context of premature birth [48, 57]. The PCL-5 [55] has 20 items with four answer options for each question (‘not at all’, ‘a little bit’, ‘moderately’, ‘quite a bit’ and ‘extremely’). The total score range is 0–80, with higher scores signifying more distress. A cut off of 31–33 [58, 59] has been proposed as indicative for probable PTSD. A 5–10 point change is likely to be the minimum threshold for a clinically meaningful difference [55]. The PCL-5 has internal consistency (for example, Cronbach’s alpha 0.95) and good construct validity in a variety of settings [58–60]. Of note, a diagnosis of PTSD requires symptoms to continue beyond 28 days after the traumatic event—therefore, in this context, the PCL-5 will measure post-traumatic stress reactions rather than PTSD.

In relation to the secondary outcomes measured at 36 weeks PMA and 4 months corrected age (F1 and F2), note that no reference is made to whether the infant is having complementary feeds (‘solids’) in addition to milk. This is because the timing of introduction of complementary feeds for premature babies is not recommended by actual age as it is with term babies, but rather personalised to the developmental stage, actual and corrected age of the infant [61].

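### Day-21 PCL-5 has no baseline mental-health covariate, although the plan intends to use baseline STAI for day-21 STAI; adding it to the PCL-5 model is an optional, nearly free gain in precision

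*Protocol article*

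**What the plan says.** In the protocol article, under Description of statistical methods, covariates are set partly for all outcomes and partly by outcome. The general rule, applied as far as feasible and with babies counted when the mother is randomised, is "Analyses will be adjusted for the stratification factors (recruiting neonatal unit, gestational age at birth and whether the participant has one or two babies alive". Two outcome-specific additions follow. One is "The STAI score at day 21 will be adjusted for the STAI score at baseline"; the other adjusts the primary outcome for the day on which the highest milk weight was measured. PCL-5 receives no addition. Crude and adjusted results are both reported, but "the primary inference will be based on the adjusted estimates".

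Under Secondary outcomes, PCL-5 appears as "Average Post-traumatic Stress Checklist for DSM-5 (PCL-5) score at day 21 (E3"), with no earlier measurement described. The same section says that a change of 5 to 10 points "is likely to be the minimum threshold for a clinically meaningful difference".

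On the availability of the covariate, the Table 2 row "Maternal mental health questionnaires" is ticked at day 21 and not in the birth-to-day-3 column. The description of the baseline form under Aim and design covers the mother herself, previous feeding experience and feeding intentions, and does not mention STAI.

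**The concern.** Unit, gestation group and number of babies do not measure maternal distress. Baseline STAI is the only baseline mental-health score that the article names, and it is assigned to one of the two distress outcomes. If baseline anxiety predicts day-21 post-traumatic stress symptoms, leaving it out of the PCL-5 model makes the interval wider than it need be. The adjusted estimate carries the inference, so the covariate list determines the PCL-5 result that readers will rely on. PCL-5 is also named in the abstract and is one of two scores behind the trial's mental-health question. What is at stake is the width of one secondary-outcome interval relative to the article's own 5 to 10 point threshold.

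**Working it through.** **The plan's own figure.** The article gives no precision or power figure for PCL-5. Its sample size is for milk yield and reproduces:

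- n per arm = 2 × (1.960 + 0.842)² × (300/155)² = 58.8, so 59 per arm and 118 in total.
- 118/0.9 = 131.1, so 132 recruited.

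The PCL-5 point does not affect these figures. They supply only the 59 per arm used below.

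**Inputs for PCL-5**

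- 59 mothers per arm: from the article's 118.
- Linear regression: "Statistical analysis of continuous outcomes will use linear regression with adjusted and unadjusted mean differences presented", with quantile regression as the alternative.
- PCL-5 SD of 15: assumed; not in the article.
- Correlation r between baseline STAI and day-21 PCL-5, given the stratification factors: assumed 0 to 0.6; not in the article.

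**Formulae**

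- SE without the covariate = 15 × √(2/59) = 2.76 points.
- SE with it = 2.76 × √(1 − r²).
- 95% half-width = 1.98 × SE.
- Power for 7.5 points (0.5 SD, the middle of the 5 to 10 range), normal approximation, two-sided 0.05.

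| r (assumed) | Fall in SE | Half-width (points) | Power for 7.5 points |
|---|---|---|---|
| 0 | 0% | 5.5 | 78% |
| 0.1 | 0.5% | 5.4 | 78% |
| 0.2 | 2.0% | 5.4 | 79% |
| 0.3 | 4.6% | 5.2 | 81% |
| 0.5 | 13.4% | 4.7 | 88% |
| 0.6 | 20.0% | 4.4 | 92% |

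The percentage fall in SE does not depend on the assumed SD; the half-widths and power do.

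**Cost of the extra term.** One degree of freedom out of roughly 110 raises the SE by about 0.5%. That cancels the gain at r = 0.1 and is negligible at r = 0.3 or more.

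**Chance imbalance.** A one-SE imbalance in baseline STAI is √(2/59) = 0.18 SD. It moves the PCL-5 difference by r × 0.184 × 15: about 0.8 points at r = 0.3 and 1.4 points at r = 0.5. The imbalance is scaled down by r.

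**Missing baseline values.** If mothers without a baseline STAI were dropped, a missing share m cancels the gain when r² = m: r = 0.22 at 5% missing and r = 0.32 at 10%. The handling of missing baselines therefore matters as much as the covariate when r is modest.

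**The case against.** The strongest reply is that nothing here is wrong. Adjusting an outcome for its own baseline, and not for another instrument's, is ordinary practice. PCL-5 has no baseline, so it gets the stratification factors, and the rule is coherent. That stands: a reader might infer that the omission has no rationale, but the own-baseline convention is an evident one.

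A reader might also infer that the PCL-5 result is biased, or that an imbalance in baseline anxiety carries over in full. The document does not support either. Under randomisation, omitting a baseline covariate from a linear model causes no bias and no inflation of type I error; the interval without the covariate already allows for chance imbalance, and only a fraction r of it carries over.

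The size is also wholly assumed. At r of 0.1 to 0.3 the gain is too small to change a reading against a 5 to 10 point threshold, and the √(1 − r²) formula does not transfer directly to quantile regression. All of this stands.

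Finally, extra covariates for one of seven secondary outcomes are often left to the SAP, and the article does not say that baseline STAI is reserved for STAI. This carries some weight. It does not dispose of the point, because the article itself names outcome-specific covariates and rests inference on the adjusted estimates. An SAP that already adds the term would settle it.

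**Conclusion.** This is an optional efficiency improvement, not an error or a contradiction in the PCL-5 analysis. As written, the comparison is valid and unbiased. For assumed correlations of 0.1 to 0.6 under linear regression, the SE would fall by about 0.5% to 20%; with an assumed SD of 15 and 59 per arm, the half-width goes from about 5.5 points to between 5.4 and 4.4. Near zero correlation nothing material changes either way. Confidence is high on what the article says and on the arithmetic, and low on where in the range the true gain lies.

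The improvement depends on a baseline STAI existing. The analysis section relies on one, while Table 2 and the baseline-form description do not list it. A reader might conclude that it is not collected. The article does not establish that, since the form's content is only summarised, but the passages need reconciling.

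**What to change.** Reword the baseline-adjustment sentence along these lines: *Day-21 STAI and day-21 PCL-5 will each be adjusted for baseline STAI, entered as a continuous term and recorded before allocation. Missing baseline values will be replaced by the overall mean, or handled with a missing indicator, so that no participant is dropped.* Fix this before the data are compared by arm, so that the covariate is not chosen after the results are seen.

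Reconcile the analysis section with Table 2 and the description of the baseline form, so that the document shows whether and when baseline STAI is taken. If it is not available before randomisation, the PCL-5 change should not be made.

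The cost is one sentence, one regression term and one degree of freedom. No data are needed beyond the baseline STAI on which the analysis section already relies, and the sample size is unaffected.
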